## Abstract

**Background:**

Mental health conditions are prevalent among Canadians and are a leading cause of disability. Each year, 1 in 5 Canadians experiences a mental health issue. A total of 5% of people aged ≥65 years perceive their mental health as fair or poor, and 6.3% of them have mood disorders. Regarding older adults with cognitive impairments such as dementia, up to 40%-50% of them experience depression at some point. We believe that older adults can benefit significantly from information and telecommunication technologies as a strategy for improving mental health conditions such as depression and anxiety, while simultaneously improving their quality of life. 3Scape Systems Inc is an Alberta-based private company that has produced a series of specialized 3D videos designed to simulate real-life events and engage individuals living with mental health disorders and cognitive impairments such as dementia.

**Objective:**

This study aims to explore the trial design and effects of 3Scape videos on older adults’ symptoms of depression and anxiety and the efficacy of this technology in improving the quality of life of patients attending the Short-Term Assessment, Rehabilitation, and Treatment Psychiatry Day Hospital program at Glenrose Rehabilitation Hospital and to provide data to estimate the parameters required to design a definitive randomized controlled trial.

**Methods:**

The trial will use a randomized controlled design comprising 15 intervention participants and 15 control group participants. The participants will be adults aged ≥65 years who are cognitively intact or have minimal cognitive impairment (ie, Montreal Cognitive Assessment score ≥18), and are clients of the Short-Term Assessment, Rehabilitation, and Treatment Psychiatry Day Hospital program at Glenrose Rehabilitation Hospital. This study’s primary outcome variables are related to clients’ depressive and anxiety symptoms and their quality of life. The control group will receive the standard of care (ie, the Short-Term Assessment, Rehabilitation, and Treatment Psychiatry Day Hospital program at Glenrose Rehabilitation Hospital). The intervention group will receive the same standard of care as the control group and will use 3Scape Systems videos for therapeutic activities.

**Results:**

Our study is currently on hold because of the COVID-19 pandemic. The recruitment process is expected to resume by November 2021, and the primary impact analysis is expected to be conducted by February 2022.

**Conclusions:**

This study will provide valuable information such as the measurement of comparative intervention effects, perception of older adults and mental health therapists about the 3Scape Systems, the associated costs of treatment, and product costs. This will contribute to the evidence planning process, which will be crucial for the future adoption of 3Scape Systems.

**Trial Registration:**

International Standard Randomized Controlled Trial Number (ISRCTN): 93685907; https://www.isrctn.com/ISRCTN93685907.

**International Registered Report Identifier (IRRID):**

PRR1-10.2196/25017

## Introduction

### Background and Rationale

Mental health disorders disrupt a person’s thinking, feeling, mood, and ability to relate to others, affecting their daily functioning. Mental health conditions are prevalent among Canadians. Mental health conditions are the leading causes of disability, with 1 in 5 Canadians experiencing a mental health concern each year. In Canada, mental health conditions are associated with high health care resource use [1,2]. In older adults, mental conditions may be aggravated by concomitant medical health issues (eg, stroke), as many of them can no longer lead active lives because of cognitive and physical decline and psychosocial factors such as isolation and poverty. According to Statistics Canada, 5% of people aged ≥65 years perceive their mental health as fair or poor [3] and 6.3% of them have mood disorders [4]. Mental health disorders contribute significantly to morbidity and mortality in older adults and reduced quality of life. Regarding older adults with cognitive impairments such as dementia, up to 40%-50% of them experience depression at some point [5]. The high prevalence of mental health conditions in Canada places a substantial burden on individuals with mental illness, caregivers, and the health care system in general. For example, by 2015, the estimated public and private mental health expenditure was Can $15.8 (US $12.7) billion, representing 7% of the total health care expenditure, and by 2022 this expenditure is expected to increase by up to 9% [2]. Reminiscence therapy is a widely used nonpharmacological psychosocial intervention in people with mental health conditions and cognitive impairments such as dementia. Reminiscence therapy involves a discussion of past events and experiences, using tangible prompts to evoke memories or stimulate conversations [6]. The literature suggests that reminiscence therapy can significantly reduce social isolation, depression, and anxiety, while simultaneously improving quality of life in older people within urban aged care settings [6-8].

We believe that older adults can benefit significantly from information and telecommunication technologies as a strategy for improving mental health conditions such as depression and anxiety, while simultaneously improving their quality of life. Information and telecommunication technologies have the potential to improve the delivery of reminiscence therapy, as these technologies facilitate access to and the selection of biographical information and related contents, or by providing novel multimodal interaction forms (eg, virtual reality) to trigger memories [9,10]. Previous investigations have studied the impact of information and telecommunication technologies on reminiscence therapy on the quality of caregiver and patient relationships, subjective patients’ well-being [11], alleviating depressive symptoms in older adults [12], and supporting social interactions in residential care [13]. 3D immersive technologies (or immersive technologies) such as virtual reality and 3D display have also been shown to have a variety of positive effects on the mental, emotional, and social health of older adults [14]. In addition, there is an opportunity to indirectly reduce caregiver and health care professional burden by delivering stimulating viewing content to older adults affected by mental health conditions, thereby enhancing their daily experience. Although these immersive technologies are slowly becoming more accessible (ie, in terms of cost), there is a lack of literature on the benefits of 3D immersion technology for the mental health well-being of seniors. As a result, whether 3D immersion technology has a positive effect on older adults’ mental health conditions and the burden of self-care remains an open question.

3Scape Systems Inc is an Alberta-based private company that has produced a series of specialized 3D videos designed to simulate real-life events and engage individuals living with mental health disorders and cognitive impairments such as dementia [15]. These videos are based on the principles of reminiscence therapy, with each video highlighting a specific topic that is present in society, including animals, music, and nature. The goals of these videos are to trigger positive memories, engage individuals, and invite comfort and familiarity. Through a series of clinical evaluations, with the aim of determining the efficacy of the 3Scape system, qualitative and quantitative data were collected to ascertain whether the use of these immersive video productions has an impact on self-care or caregiver burden, the use of antipsychotic medications, mood, agitation, emotion, engagement, tolerability of 3D intervention, satisfaction with life, and the quality of life of older adults with and without cognitive impairment [16]. However, there were important threats to the internal validity of these studies, as there were no control conditions or groups; thus, the quality of evidence provided was very low.

### Evaluation Objectives and Research Questions

This study aims to explore the trial design and effect of 3Scape videos on older adults’ depressive and anxiety symptoms and quality of life and the efficacy in terms of caregiver burden of the Short-Term Assessment, Rehabilitation, and Treatment Psychiatry Day Hospital program at Glenrose Rehabilitation Hospital and to provide data to estimate the required parameters to design a definitive randomized controlled trial (RCT). Thus, this study has the following five research questions:

Is the designed protocol feasible for conducting a future definitive RCT?Do the 3Scape videos affect older adults’ depressive and anxiety symptoms, mood, and overall quality of life compared with clients who receive the standard of care?What are the overall experiences, beliefs, and attitudes of older adults while watching 3Scape videos?What are the overall experiences, beliefs, and attitudes of therapists while watching 3Scape videos?Do 3Scape videos affect caregivers’ burden compared with the same caregivers who provide the standard of care?

## Methods

### Study Design

This study will use a multimethod research design. The *Methods* section is presented in accordance with the study’s research questions. Additional details have been provided in Figure 1.

**Figure 1 figure1:**
[figure not shown]
Study components. GRH: Glenrose Rehabilitation Hospital; HoNOS: Health of the Nation Outcome Scale; MoCA: Montreal Cognitive Assessment; OPQoL-Brief: Older People’s Quality of Life-Brief; RCT: randomized controlled trial.

Research questions 1-3, feasibility parallel-group RCT: The experimental group will receive the intervention, which consists of sessions with the 3Scape videos, whereas the control group will receive the standard of care used at the Short-Term Assessment, Rehabilitation, and Treatment Psychiatry Day Hospital program at Glenrose Rehabilitation Hospital (see the *Outcome Variables* section for more details). For this pilot study, we will follow the CONSORT (Consolidated Standards of Reporting Trials) guidelines for randomized feasibility studies [17]. The *Methods* section is presented with regard to the objectives of the study.Research question 4, study design: qualitative description design [18].Research question 5, study design: quantitative descriptive [19].

### Study Setting

This study will be conducted at the Short-Term Assessment, Rehabilitation, and Treatment Psychiatry Day Hospital at Glenrose Rehabilitation Hospital located in Edmonton, Alberta, Canada.

### Eligibility Criteria

#### Inclusion Criteria

The study participants will include adults aged ≥65 years attending the Short-Term Assessment, Rehabilitation, and Treatment Psychiatry Day Hospital program at Glenrose Rehabilitation Hospital who are cognitively intact or with minimal cognitive impairment; that is, Montreal Cognitive Assessment score ≥18 [20].

#### Exclusion Criteria

Potential participants who are unable to provide informed consent, are unable to communicate in the English language, have a significant sensory impairment (which would prevent adequate viewing of the 3D videos), have a mental health diagnosis with behavioral disturbances such as the potential for aggression or severe agitation, with aphasia, or other diagnoses that would prevent the participant from completing surveys, or have posttraumatic stress disorder or zoophobia will be excluded.

### Interventions

The eligible participants will be randomly assigned 1:1 to either the experimental group or the control group.

#### Control Group

This group will receive standard care consisting of (1) standard psychiatric nursing care (including some individual counseling), (2) medication trials or titration (antidepressants, antianxiety medicines, sleep medicines), and (3) group therapies (psychoeducation, cognitive behavioral therapy, stress management groups, dialectical behavior therapy, exercise groups, community engagement and wellness groups, leisure groups, and grief and loss groups). Every group runs twice a week for 6 weeks (1.5 months). The patients simultaneously attend 3 therapy groups for 6 weeks. That is, the patients attend 3 therapy sessions per day, twice a week. Each patient attends every group at some point during their 20-week stay in the program. Each group session is 1 hour long. Therefore, the patients receive 36 hours of standard care every 6 weeks for a total of 108 hours on the Short-Term Assessment, Rehabilitation, and Treatment program.

#### Experimental (Intervention) Group

In the experimental arm, the psychoeducation (Leisure Choices) group therapy (on the Short-Term Assessment, Rehabilitation, and Treatment program) will be replaced by five 3D video screenings (the intervention); in addition, they will receive the same standard care. The five 3D video screening sessions will be delivered as one session per week within a 6-week time frame. Each session will take approximately 1 hour, consisting of one 20-minute video screening and a postvideo screening discussion and questionnaire. A therapist and a member of the research team will be present during the video screening sessions. The therapist will lead the video screening sessions and the postvideo screening discussion (20 minutes of video and 20 minutes of discussion). The research team will observe alertness during video screenings sessions. After the discussion, the research team will administer two questionnaires (Positive and Negative Affect Schedule [PANAS] and postscreening survey), which will take approximately 20 minutes. Each session will take 1 hour overall. The videos will be screened in any order. The goal of these videos is to trigger positive memories, engage individuals, and bring comfort and familiarity. The topics of the videos are as follows: (1) *The Path*, (2) *Remembering*, (3) *The Dance*, (4) *The Memory Box*, and (5) *Baby Animals*. A sample of the videos can be found on the company’s website [15]. The sessions will take place at the Courage Center at Glenrose Rehabilitation Hospital. No more than 5 participants will be present during each video screening session.

### Outcome Variables

#### Research Questions 1-2 (Primary Outcome Variables)

Older adults’ depressive and anxiety symptoms, mood, overall quality of life, and engagement are the primary outcome variables for these research questions. Older adults’ depressive and anxiety symptoms will be assessed using the Generalized Anxiety Disorder-7 item (GAD-7) scale patient self-report tool [21] and the Health of the Nation Outcome Scale (HoNOS; a clinician rating tool) symptoms [22], older adults’ mood will be measured using PANAS (20-item self-report questionnaire) [23], and older adults’ overall quality of life will be measured using Older People’s Quality of Life-Brief (OPQoL-Brief) questionnaire scale-13 items self-reported tool [24].

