### Sample Size

#### Research Questions 1-3 (Participants: Older Adults)

As this is a feasibility study, a sample size calculation is not required [17]. However, we can estimate the number of participants we will be able to recruit during the data collection period. In this feasibility study with a statistical power of 0.8, an α of .05, and an effect size of 1.20, the minimum required sample size will be 24 participants in total (12 in each group [19]). We aim to recruit 15 participants for each group, for a total sample size of 30, to compensate for a 20% dropout rate. Sample size calculations are estimated using G*Power (version 3.1.9.4, Universitat Kiel) [29].

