### Data Analyses

#### Research Questions 1, 2, and 3

The analyses will be conducted in SPSS using intention-to-treat principles. Descriptive statistics will be used to characterize the groups during the pretest. Owing to the small sample size, comparisons of the GAD-7, HoNOS, OPQoL-Brief, and PANAS scores within the groups will be performed using a Wilcoxon signed-rank test (*P*≤.05), and comparisons between the groups will be calculated using the Mann–Whitney *U* test (*P*≤.05). The GAD-7, HoNOS, OPQoL-Brief, and PANAS scores will be used to analyze the clinical significance, established as a change of 2 or more units [30]. Participants’ engagement will be analyzed using descriptive statistics.

#### Research Question 4

The audiotapes will be transcribed and content analysis will be performed. The content analysis will be data driven. Data codes will be inductively generated using the data collected. Through the coding, a small number of themes or categories will be generated. The analyses will be performed by an RA, and a consensus in the interpretations will be achieved through a discussion among the research team members. The validity of the interpretations will be discussed with and agreed upon by every member of the research team. NVivo 10 software will be used to conduct data analysis.

#### Research Question 5

Descriptive statistics will be used to characterize the groups at pretest and posttest. Owing to the small sample size, comparisons of the MBI-HSS MP scores within the groups will be performed using a Wilcoxon signed-rank test (*P*≤.05), and comparisons between the groups will be calculated using a Mann–Whitney *U* test (*P*≤.05).

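### Four primary scales are each tested at P≤.05 with no lead scale or success rule, and the one power figure names neither a scale nor a test

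*Protocol article*

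**What the plan says.** Under Outcome Variables, the primary paragraph for research questions 1-2 reads: "Older adults’ depressive and anxiety symptoms, mood, overall quality of life, and engagement are the primary outcome variables for these research questions". It assigns GAD-7 and HoNOS to symptoms, PANAS to mood and OPQoL-Brief to quality of life. Table 1 lists these four scales as primary. Engagement is also listed as secondary in the next paragraph and is only described in the analysis, so it adds no test.

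Under Data Analyses (research questions 1, 2 and 3), "comparisons of the GAD-7, HoNOS, OPQoL-Brief, and PANAS scores within the groups will be performed using a Wilcoxon signed-rank test", and between-group comparisons of the scores use the Mann-Whitney U test. Both carry a threshold of P≤.05. No scale is put first, no rule says what pattern of results would count as an effect, and no adjustment is given.

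The Sample Size section says that a feasibility study needs no calculation, then gives one: "with a statistical power of 0.8, an α of .05, and an effect size of 1.20, the minimum required sample size will be 24". It continues: "We aim to recruit 15 participants for each group, for a total sample size of 30, to compensate for a 20% dropout rate". It names the software (G*Power) but no scale, test or sidedness.

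The article is inconsistent on PANAS. Table 1 marks it for both arms at T0, T1 and T8. Data Collection Methods has it given to intervention participants after each video session, and names only the other three scales for both arms.

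**The concern.** Several co-equal primary scales, each with its own 5% test, leave open which result answers research question 2 (whether the videos affect symptoms, mood and quality of life). A reader who takes any one significant scale as an effect accepts a false-positive chance well above 5%. The within-arm tests add up to eight more P≤.05 readings (four scales in two arms) for each pair of time points compared, and none of them compares the arms.

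The power statement does not settle the matter. One pair of figures, 80% and .05, cannot describe four primary scales unless the plan says which scale it belongs to, and it appears to rest on a different test from the one planned.

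This matters even in a feasibility trial. The article speaks of efficacy in its objective, announces a primary impact analysis, and links the comparative effects to future adoption of the product. The protocol itself fixes the primary set, the tests and the threshold, so this is not merely detail left to an analysis plan that is not shown.

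**Working it through.** **Inputs from the protocol article.** Power 0.80, α .05, effect size 1.20, 12 per group, 20% dropout, 30 recruited (Sample Size); 1:1 allocation (Interventions); four tested primary scales (Outcome Variables, Table 1); Mann-Whitney between groups at P≤.05 (Data Analyses).

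**Assumptions.** Two-sided testing, normally distributed scores, and equal correlation between scales. The documents give none of these.

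**1. The plan's own figure.** For a two-sample t-test with n per arm, the noncentrality is d·√(n/2) on 2n − 2 degrees of freedom.
- n = 12: 1.20 × √6 = 2.939; df = 22; two-sided critical value 2.074; power 80.2%.
- n = 11: power 76.3%, so 12 is the minimum.
- A one-sided t-test would need only 10 per arm, so the stated 12 points to a two-sided t-test.
- Dropout: 24 / 0.80 = 30. If the planned 20% are lost, 15 × 0.80 = 12 per arm remain.

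The stated figure therefore reproduces.

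**2. The planned test.** For normal data the Mann-Whitney test has asymptotic relative efficiency (ARE) 3/π = 0.955 against the t-test. The same formula is used with n replaced by 0.955n.
- 12 per arm: effective n = 11.46; noncentrality 1.20 × √5.73 = 2.872; power 78.2%.
- Exact Mann-Whitney at 12 per arm, by simulation: about 76.5-77%.
- 13 per arm: 81.6%, so 26 evaluable.
- 15 per arm, with no dropout: 87.2%.
- Effect size giving 80% at 12 per arm by the ARE method: d = 1.228, about 1.23.

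The shortfall against 80.2% is about 2 to 4 percentage points.

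**3. Chance of at least one false-positive between-arm result.** For m independent tests at .05 this is 1 − 0.95^m.
- m = 4: 1 − 0.8145 = 18.5%.
- m = 3 (controls without PANAS): 1 − 0.8574 = 14.3%.

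With correlated scales, by multivariate normal simulation:

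| Assumed correlation | Four scales | Three scales |
|---|---|---|
| 0 | 18.5% | 14.3% |
| 0.5 | about 16% | about 12.5% |
| 0.7 | about 13% | about 11% |
| 0.9 | about 9% | about 8% |

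The exact Mann-Whitney test at 12 per arm is slightly conservative (about 4.5% per test). For four scales its simulated range is 17.0% at correlation 0 to 9.2% at 0.9. Every case is above 5%.

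**The case against.** The strongest reply is that the protocol never claims what it would be faulted for missing. The .05 appears as an input to the sample size and as a per-test threshold, never as a trial-wide error rate, and 80% is nowhere said to cover all four scales. The article calls feasibility its primary objective, says that no calculation is required, and aims to supply parameters for a definitive trial. The t-test is an inference from the arithmetic. All of this stands, and it limits the point.

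A reader might infer that the trial has neither a 5% error rate nor 80% power. The documents do not support that. The two failures rest on different success rules. If any one scale suffices, the error rate is inflated, but unadjusted power for at least one scale is 87% to 99.7% (d = 1.20 on all four, correlation 0.9 down to 0). If one named scale decides, the error rate is at most 5% and power is about 77-78%.

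Nor is the drop to about 56% power per scale at α = .05/4 a flaw in the plan, since the plan makes no such adjustment. Counting PANAS as two tests has no basis either: the article describes one 20-item questionnaire and plans no separate scores.

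What the reply does not answer is that the article still plans significance tests on four co-equal primary scales and attaches one power figure to none of them.

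**Conclusion.** The point holds in a limited form. Four primary scales are each tested at P≤.05 with no lead scale, success rule or adjustment. If any one significant between-arm result is read as an effect, the false-positive chance is between 9% and 18.5%, or between 8% and 14% if controls have no PANAS. These ranges rest on assumed correlations from 0.9 down to 0. Anxiety, mood and quality-of-life scores are unlikely to be independent, so the top of each range is an upper guide.

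The power mismatch is minor: 80.2% for the inferred t-test against about 77-78% for the planned Mann-Whitney test at 12 per arm with normal data. One more evaluable participant per arm would remove it by the ARE method. The more important gap is that the figure is tied to no scale.

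**What to change.** In Outcome Variables and Data Analyses, name one lead scale that is measured in both arms, and name its week-18 (T8) between-arm comparison as the lead analysis. Report the other scales, and all within-arm changes, as estimates with 95% confidence intervals and without a P≤.05 claim. State whether controls complete PANAS, so that Table 1 and Data Collection Methods agree.

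In Sample Size, restate the figure along these lines: 24 evaluable participants give about 77-78% power for d = 1.20 by an unadjusted two-sided Mann-Whitney test on the lead scale only, assuming normal data; 80% power corresponds to d of about 1.23 (ARE method). If the lead analysis adjusts for the T1 score, describe this as the unadjusted figure, since it does not give the power of the adjusted analysis.

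The change needs wording only, with no extra participants or staff. The cost is a slightly lower stated power and the loss of test status for the non-lead scales. Estimates with intervals also suit the stated aim of supplying parameters for a definitive trial.

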#### Research Questions 1-2 (Secondary Outcome Variables)

Engagement while watching the 3Scape videos will be measured using an engagement scale developed by team members in a previous study [25]. This is an 8-point Likert scale that has been shown to be understood by older adults, even those with mild cognitive impairments.

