## Discussion

### Principal Findings

The primary objective of this proposed study is to assess the feasibility of conducting a definitive trial on the effectiveness of 3Scape technologies. The results of this project will inform the development of best practices for older adults with mental health conditions such as depression and anxiety, which affect as much as 6.3% of the population of older adults. Currently, our study is on hold because of the COVID-19 pandemic. The recruitment process is expected to resume by November 2020, and the primary impact analysis is expected to be conducted by February 2021.

The level of evidence that immersive technologies have an impact on older adults’ mental health conditions and the burden of care is low. The 3Scape Systems Inc videos have the potential to become a sound alternative at the midpoint between these 2 extremes. 3Scape Systems has a technological readiness level of 9 [31], thus having a sufficient level of readiness that can be tested in a real-world clinical setting. This feasibility study is the first RCT to evaluate the potential benefits of 3Scape Systems. Conducting this RCT will provide valuable information. First, the estimates can be used for sample size calculations in future RCTs. Second, as we will measure the patients’ outcome variables on 4 different occasions during the intervention, the results of this study will guide therapists on the expected percentage of a patient’s improvement and how progress was achieved over a period of 10 weeks. The results of this project will provide them with information on the feasibility of adopting 3Scape Systems.

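### Feasibility is the stated primary objective and first research question, but the primary outcomes and analysis assigned to it are clinical, and engagement is listed as both primary and secondary

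*Protocol article*

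**What the plan says.** Objective. Under Principal Findings the article states: "The primary objective of this proposed study is to assess the feasibility of conducting a definitive trial on the effectiveness of 3Scape technologies". The first item in Evaluation Objectives and Research Questions is "Is the designed protocol feasible for conducting a future definitive RCT", and Study Design labels questions 1 to 3 a feasibility parallel-group RCT.

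Primary outcomes. The subsection on primary outcome variables covers research questions 1 and 2 together. After depressive and anxiety symptoms it continues: "mood, overall quality of life, and engagement are the primary outcome variables for these research questions". The Abstract (Methods) also describes the primary outcomes as symptoms and quality of life. Table 1 lists GAD-7, HoNOS, OPQoL-Brief and PANAS as primary.

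Analysis. Data Analyses has a single subsection for questions 1, 2 and 3. It sets Wilcoxon signed-rank tests within groups and Mann-Whitney tests between groups on those four scales, each at P≤.05, and a two-unit threshold for clinical significance. For the remaining measure, "engagement will be analyzed using descriptive statistics".

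Engagement. The next outcome subsection, headed as secondary for the same two questions, says: "Engagement while watching the 3Scape videos will be measured using an engagement scale". Table 1 also places engagement among the secondary outcomes and marks it for the intervention group only.

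**The concern.** A trial's primary outcome should answer its primary objective. Here the objective is whether a definitive trial can be run, while every primary outcome attached to that question describes the patient's clinical state or response to the videos. A team following the article would complete its primary analysis without having reported recruitment, retention, attendance or completeness as results.

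Two further problems follow. Four scales are tested at the same level with no main scale named, so one P≤.05 by chance could become the headline of a study too small to support it. And engagement cannot be both primary and secondary. Because it refers to watching the videos and is recorded in one arm, it cannot be a between-arm outcome at all.

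**Working it through.** **1. Objective against outcome.**

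| Item | Where | Content |
|---|---|---|
| Primary objective | Principal Findings | Feasibility of a definitive trial |
| Question 1 | Evaluation Objectives and Research Questions | Feasibility of the protocol |
| Primary outcomes, questions 1-2 | Outcome Variables | Symptoms, mood, quality of life, engagement |
| Primary outcomes | Table 1 | GAD-7, HoNOS, OPQoL-Brief, PANAS |
| Analysis, questions 1-3 | Data Analyses | Tests at P≤.05 on four scales; engagement descriptive |

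The last three rows contain no measure of whether a trial can be run.

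**2. The article's own sample size.** Inputs from Sample Size: power 0.8, α .05, effect size 1.20, 20% dropout. A two-sided two-sample t-test (two-sidedness assumed) needs n = 11.94, so 12 per group (power 0.802) and 24 in total. Then 24 / (1 − 0.20) = 30. The figure reproduces and is not in dispute. It is, however, sized for a test on an unnamed clinical scale. With 12 per group, the same t-test has 47% power at an effect size of 0.8 and 22% at 0.5, so a P value on a clinical scale settles little in either direction.

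**3. Chance of at least one false positive.** Inputs: four between-group tests at one time point, each at .05, with no effect on any scale.

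- Independent scales: 1 − 0.95^4 = 1 − 0.8145 = 18.5%.
- The article gives no correlation between scales, so a range is assumed. Simulated exact Mann-Whitney tests with 12 and with 15 per arm (200,000 draws each) give about 17% at correlation 0, 16% at 0.3, 14% to 15% at 0.5 and 12% at 0.7. At correlation 0 the result is below 18.5% because the exact test has an actual size of about 0.045: 1 − (1 − 0.045)^4 = 16.8%.
- The count of four follows Table 1, which shows PANAS in both arms. Data Collection Methods describes PANAS only after the video sessions. If it were not compared between arms, three independent tests would give 1 − 0.95^3 = 14.3%.

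**4. What 30 participants can say about feasibility.** The planned 20% dropout corresponds to 24 of 30 completing, or 80%. The exact 95% CI is 61% to 92% (Wilson 63% to 90%). That is wide, but it bears directly on question 1.

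**The case against.** The strongest reply is that the trial will still produce feasibility information. It commits to the CONSORT guidelines for feasibility studies, questions 3 and 4 collect participant and therapist experience, one stated aim is to estimate parameters for a definitive RCT, and recruitment and dropout can be counted from ordinary records. A journal article may also leave progression cut-offs and a multiplicity rule to a fuller document. Most of this stands. A reader might infer that the trial cannot say anything about feasibility, and that goes too far. What remains is that the article does not leave the primary outcomes of question 1 open: it fixes them, and they are clinical.

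Other stronger readings are tempting but unsupported:

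- That P values will decide feasibility. The shared heading in Data Analyses allows this reading, but no sentence says it. The tests may be meant for question 2 alone.
- That all the listed primary outcomes are tested. Engagement is only described.
- That the observed effect will size the next trial. The article says "the estimates can be used for sample size calculations in future RCTs", and estimates may just as well mean the SD and the dropout rate.
- That the false-positive chance is 22.6% (five independent scores) or 46% (adding eight within-group tests). The first assumes PANAS is split into two scores, which the article does not state. The second treats change over time as a treatment effect, although patients in standard care may change too.

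**Conclusion.** The point holds as a contradiction within the article. The stated primary objective has no matching primary outcome or analysis, because question 1 has been given the outcomes of question 2. The double listing of engagement is a separate, plain inconsistency.

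The multiplicity cost is moderate: 18.5% against a nominal 5% if the four scales are independent, and about 12% to 16% under assumed correlations of 0.7 down to 0.3. It rests on four between-group comparisons at one time point and no true effect. It adds to the case, but the misassignment would need correcting even if only one scale were tested.

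**What to change.** 1. For question 1, make feasibility measures primary: the number recruited among those eligible and approached, T8 completion by arm, session attendance, and completeness of each scale. Report each with a 95% CI against progression criteria that the team sets before recruitment resumes. The cut-offs are the team's choice. Count withdrawn participants in the completion denominator, since the section on withdrawal removes their information from the analysis.
2. Assign GAD-7, HoNOS, OPQoL-Brief and PANAS to question 2 as secondary or exploratory, reported as between-arm differences with 95% CIs. If a test is kept, name one main scale at T8.
3. List engagement once, as a descriptive measure in the intervention arm.
4. Bring the Abstract, Outcome Variables, Table 1 and Data Analyses into line.

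The cost is mostly wording and agreeing the criteria. The counts come from screening, attendance and completion records and need no further patient assessments. The trial gives up an efficacy claim from about 30 people. Because it is already approved, registered and launched, changing the primary outcomes may also require an ethics amendment and a registry update.
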